**Methods:**

In this ambispective intervention cohort study,1,200 patients with CKD stages 1–5 will be recruited from July 2015 to July 2024 in 3 branches of Guangdong Provincial Hospital of Chinese Medicine (GPHCM) in Guangdong province, China. The patients in the self-management cohort will choose to receive an intervention that consists of education, nutrition/diet modification, lifestyle change recommendation, medication review, and psychology support based on Social Cognition Theory (SCT). The patients in the control cohort will do regular follow-ups based on the clinic rules. All the patients will be followed up for 5 years, or until the occurrence of a primary outcome. Detailed clinical, laboratory markers, nutritional status, psychological exposures and outcome questionaries will be collected semiannually in CKD stage 1–2 and trimonthly in stage 3–5 patients. The primary outcome is the occurrence of composite clinical endpoints (doubling of serum creatinine level, ESKD, loss of renal function (≥ 40% decline in GFR from baseline), death, major cardiovascular or cerebrovascular events). The main secondary outcomes include the absolute change and slope of eGFR, absolute changes of urinary protein creatinine ratio, 24-h urine proteinuria, intact parathyroid hormone level, and self-management adherence rate and quality of life from baseline to end of the study. The effectiveness of self-management will be analyzed and the association between longitudinal trajectories of self-management and renal outcomes will be evaluated.

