## Methods

### Study design and study population

An ambispective cohort study will be conducted in the department of nephrology at the three branches of Guangdong Provincial Hospital of Chinese Medicine (GPHCM) in Guangdong province, China. Two branches are located in different Districts in Guangzhou city (Yuexiu and Fangcun District) and one in Zhuhai city. The study population includes all CKD 1–5 patients (speak Cantonese or Mandarin) attending the CKD consultation outpatient clinic in GPHCM from July 2015 to July 2024. Of 200 CKD patients were already registered in the retrospective cohort from July 2015 to July 2019 and they will keep following in the prospective cohort. Beginning in August 2019, a prospective cohort will be built on. All the patients will be followed for at least 5 years, or until the occurrence of a primary outcome.

CKD is defined by a glomerular filtration rate (GFR) < 60 mL/min/1.73 m2 or markers of kidney damage, or both, of at least 3 months duration [5]. GFR is calculated by CKD-EPI equation, and CKD staging will use the Kidney Disease Outcomes Quality Initiative (KDOQI) definition [29]. Patients are eligible for inclusion if they are Chinese, aged 18 to 80 years, have CKD (Stages 1–5), and give a written signed informed consent. Exclusion criteria for the study are psychosis or unable to cooperate with clinical staff for other reasons and have a history of dialysis or renal transplant.

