### Screening and Enrollment

Research assistants in our team are responsible for identifying patients from retrospective cohort and consultation outpatient in the Department of Chronic Disease Management at GPHCM to ensure they meet inclusion criteria. Considering the retrospective cohort is an observational cohort, this study will use the date when the patients are enrolled in the new cohort as their baseline time. After pre-evaluation, nurses will first make an appointment and then explain the study to candidates through a face-to-face interview and answer any questions they have. If the patients do not agree to enroll in SMP-CKD cohort, they will be registered in the chronic disease management clinic in GPHCM and do regular follow-up based on the clinic rules (as the control cohort). After confirming eligibility, all participants will sign an informed consent. (Study process can be found in Fig. 1).

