## Sample size calculation

We selected the occurrence of composite endpoints as the primary study outcomes to calculate the sample size. Previous studies have reported that the composite endpoints rate range from 18.1–126/1,000 person-years [46, 47]. Based on these studies and our previous data, we estimated that the incidence rate of a composite endpoint in our cohort would be 60/1,000 person-years. There are about 30 variables that may affect prognosis, and there should be at least 10 endpoints per variable. Thus, we anticipate that recruiting 1,200 participants with 300 events over a 5-year follow-up will ensure adequate statistical power.

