## Statistical analysis plan

Categorical demographic and other baseline characteristics variables will be summarized by frequencies and percentages. Continuous variables will be summarized by both mean and standard deviation for data with normal distributions or median and inter-quartile range for non-normally distributed data. Either a Chi-square or Fisher’s exact test will be used to compare categorical variables between groups, while Mann–Whitney U-test or Student’s t-test will be used for continuous variables, if necessary.

The primary objective of this cohort is to evaluate the effectiveness of the self-management program, we plan to perform three separate analyses for the primary outcome. First, the incidence rate of composite endpoint events will be analyzed by the Chi-squared test. Second, time to occurrence of composite clinical endpoints will be analyzed using log rank test. The hazard ratio (HR) with 95% CI will be estimated by using the Cox proportional hazards model or competitive risk model. Third, growth mixture models and group-based trajectory models (GBTM) will be used to analyze the trajectories of exposure and outcome variables [48]. Covariates for the models will be selected based on prior knowledge and published papers. Logistic regression or Poisson regression will be used to analyze categorical outcomes. Liner mixed-effect model will be applied to the longitudinal data, such as the absolute change, and slope of eGFR and other secondary outcomes.

Even with some retention strategies, considerable missing data is expected over 5-years follow-up. The proportion of missing data will be summarized in each group and at each visit point. If there is less than 20% of data missing for the covariate data, we will perform a complete case analysis. If there is more than 20% of missing data, we will perform Little’s test and use multiple imputations under the assumption of missing is at random. Subgroup analyses will be conducted across baseline eGFR levels, demographic status and other factors, if possible. To test the credibility and robustness of the findings, several sensitivity analyses will be performed, including E-value and other advanced models [49]. Effect modification will be investigated using stratified analyses and formal tests of interaction. Mediation will be analyzed by adding the hypothesized mediators, one by one, to the confounder-adjusted models to study the extent to which they explain any association found.

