Since self-management is a complex intervention, how to deliver a reasonable self-management intervention is still being explored [60]. We use process evaluation to provide novel information and understanding about how self-management works in clinical practice. Process evaluation will evaluate the components of execution, the influence mechanism and context to identify and understand the core components of self-management [61]. This not only can increase understanding of how the process is delivered, but also help us derive more reliable conclusions about the effectiveness of interventions in terms of whether they can be accepted by patients and healthcare professionals [62].

However, this study has some limitations. Firstly, potential selection bias or confounder effect may exist because it is a hospital-based design study, the results may not sufficiently generalize to other populations. But we try to select 3 branches hospitals, while the source populations of these three hospitals have different demographic and socioeconomic characteristics, it can increase the confidence in the generalizability of the study. And more so than other cohorts, its hospital-based design can ascertain that CKD patients’ diagnoses and the interpretations of the renal outcomes are accurate which means the risk of misclassification bias is low [63]. Secondly, the long study period is a double-edged sword. Although a considerable amount of follow-up data can be obtained during the study which allows us to have the possibilities to dynamically evaluate patients’ condition and study the relationship among longitudinal trajectories of exposure, surrogate markers, and renal outcomes [48]. High rates of patient's lost-to-follow-up are inevitable, how to minimize the drop-outs and deal with the missing data is a big challenge. One solution is the patients enrolled in this cohort are registered in the chronic disease management clinic in GPHCM, they will return to the outpatient clinic for regular checkups because we are the designated hospital for patients' medical insurance. The other solution is some retention strategies have been adopted, such as reducing barriers to participation, setting reminder strategies and gift/freebies incentives.

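### The log-rank test on the primary outcome names no branch strata although patients choose the programme and the three branches serve different populations; if both uptake and risk differ by branch, the test is confounded

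*Protocol article*

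**What the plan says.** The Statistical analysis plan section lists three analyses of the composite primary outcome. The first is a chi-squared test. In the second, "time to occurrence of composite clinical endpoints will be analyzed using log rank test", followed by a hazard ratio from a Cox or competing-risk model. The third is trajectory modelling. Model covariates are to be chosen from prior knowledge and the literature; branch is not named among them, nor as a stratum, subgroup or interaction term.

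Exposure is not assigned. The Abstract (Methods) states: "The patients in the self-management cohort will choose to receive an intervention". Screening and Enrollment gives the source of the controls: "If the patients do not agree to enroll in SMP-CKD cohort, they will be registered in the chronic disease management clinic in GPHCM", where they have routine follow-up.

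The study runs at three sites: "Two branches are located in different Districts in Guangzhou city (Yuexiu and Fangcun District) and one in Zhuhai city". In the Discussion, the authors support generalisability by noting that "the source populations of these three hospitals have different demographic and socioeconomic characteristics". The same paragraph concedes possible selection bias or confounding.

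**The concern.** In a randomised trial, leaving site out of a log-rank test costs mainly efficiency, because allocation balances site. Here nothing balances branch between the cohorts. A branch whose patients join more readily and also have lower risk supplies more programme patients and fewer events, and a pooled test credits that difference to the programme. With the opposite pattern, a real benefit is diluted or reversed.

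A log-rank test takes no covariates, so the later promise to select covariates for the models cannot repair it. Its p-value stands as a separate primary-outcome result and could disagree with the adjusted hazard ratio. The article does not say which of the two would lead.

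**Working it through.** **1. The plan's own figure.** The Sample size calculation section uses about 30 variables at 10 events each: 30 × 10 = 300 events. It also states that "we estimated that the incidence rate of a composite endpoint in our cohort would be 60/1,000 person-years". At a constant hazard of 0.06 per year, 1,200 patients followed for 5 years give 1,200 × (1 − exp(−0.30)) = 311 events. With exponential loss at rate m, where m = −ln(1 − d)/5 for five-year loss d, the count is 1,200 × 0.06/(0.06 + m) × (1 − exp(−5(0.06 + m))). This is 304 for d = 5% and 296 for d = 10%. So 300 is reproduced with modest loss, and the checks below use this scale.

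**2. Assumptions.** The article gives no branch sizes, uptakes or event rates. I assume 400 patients per branch, constant hazards, 5 years without loss, and no programme effect within any branch. Assumed rates average 60 per 1,000 person-years. They lie inside the cited range ("the composite endpoints rate range from 18.1–126/1,000 person-years"), but that range is between published studies, so it does not show how far these branches differ.

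**3. Crude rate ratio.** For branch j with uptake p and hazard h, programme events are 400·p·(1 − exp(−5h)) and programme person-years are that number divided by h. Controls use 1 − p.

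Strong case: uptake 70/50/30%, rates 40/60/80 per 1,000.
- Programme (280, 200, 120 patients): events 50.8 + 51.8 + 39.6 = 142.2; person-years 1,268.9 + 863.9 + 494.5 = 2,627.3; rate 54.1 per 1,000.
- Control (120, 200, 280 patients): events 21.8 + 51.8 + 92.3 = 165.9; person-years 543.8 + 863.9 + 1,153.9 = 2,561.6; rate 64.8 per 1,000.
- Ratio 54.1/64.8 = 0.84. Reversing uptake to 30/50/70% gives 1/0.835 = 1.20.

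The same steps give 0.915 for uptake 70/50/30% with rates 50/60/70, and 0.956 for uptake 60/50/40% with rates 50/60/70.

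**4. Effect on the test.** Each scenario was simulated 4,000 times (two-sided 5%), comparing the pooled log-rank test with the test stratified by branch.

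| True HR | Rates per 1,000 | Uptake, % | Pooled rejects | Stratified rejects | Pooled HR |
|---|---|---|---|---|---|
| 1.00 | 50/60/70 | 60/50/40 | 6.6% | 5.2% | 0.96 |
| 1.00 | 50/60/70 | 70/50/30 | 13.5% | 4.7% | 0.91 |
| 1.00 | 40/60/80 | 60/50/40 | 13.1% | 5.1% | 0.91 |
| 1.00 | 40/60/80 | 70/50/30 | 34.6% | 5.2% | 0.84 |
| 0.70 | 50/60/70 | 30/50/70 | 59.0% | 79.5% | 0.76 |
| 0.70 | 40/60/80 | 30/50/70 | 28.0% | 77.9% | 0.84 |

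With no true effect, if either uptake or risk is equal across branches, the pooled test rejects in 4.2% to 5.6% of runs, so it keeps its level. With equal uptake and a true HR of 0.70, rates 40/60/80 give 82.5% power pooled and 82.4% stratified, so stratifying costs almost nothing when it is not needed.

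The stratified test recovers the true value by construction, because no self-selection within branches was simulated.

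**5. What branch-specific results can bear.** 300 events over three branches is about 100 each. With equal arms, SE(log HR) = √(4/100) = 0.20. An observed HR of 0.70 then has a 95% interval of 0.70 × exp(±1.96 × 0.20), about 0.47 to 1.04.

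**The case against.** The strongest reply is that this is a condensed article. Strata and covariate lists commonly sit in a fuller plan, which is not shown, and the article never says that branch is excluded. It plans a Cox or competing-risk model with selected covariates, E-values, subgroups by demographic and other factors, and interaction tests; branch could enter any of these. That stands. A reader might infer that branch is ignored throughout, or that no result will be compared between branches. The text is silent on this and does not support either reading. What remains is that the article fixes a log-rank test, with no strata named, as a separate analysis in a self-selected, three-branch cohort, and none of those model plans alters that test.

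A reader might also suppose that branches differ in staff practice or record keeping. The article points the other way: team members attend a common training workshop, creatinine doubling is judged by a central laboratory, and outcomes are taken from the hospital's information system. The concern rests only on the stated population differences.

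It is also fair to say that uptake by branch is unknown, and that the strong case needs a two-fold gradient in risk and a 40-point gradient in uptake, in exactly opposite order. In the mild case the test is barely disturbed. Finally, self-selection operates inside every branch, so stratifying by branch leaves confounding by patient characteristics untouched.

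**Conclusion.** The point holds as a conditional weakness. Followed as written, the log-rank test is open to confounding by branch in either direction, and this needs both uptake and event risk to vary by branch. The article supports a difference in populations but reports neither quantity, so the actual bias cannot be stated. Under the assumptions above, the null-effect crude ratio runs from 0.96 to 0.84, and false rejection from 6.6% to 34.6%.

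These figures describe an unadjusted comparison. They do not show that the Cox or competing-risk hazard ratio is biased, since it may yet adjust for branch; the article simply does not commit to it. Nor do they show that a branch-stratified test would be free of confounding.

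A reader might go further and ask that the generalisability statement be made to depend on a programme-by-branch interaction test. That is not supported. The Discussion's claim is hedged and concerns breadth of sampling, and about 100 events per branch are too few for a non-significant interaction to show consistency.

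**What to change.** - Stratify the log-rank test and the Cox baseline hazard by branch (three strata). If the competing-risk model is used, commit to branch there too.
- Include branch as a fixed effect in the linear mixed models and in any propensity model.
- Name the confounder-adjusted hazard ratio as the main primary result, with the log-rank and chi-squared tests as supporting, because branch strata do not deal with self-selection within a branch.
- Tabulate uptake and event rates by branch, so that readers can see whether the condition for bias was met.
- Report branch-specific hazard ratios and the programme-by-branch interaction with intervals, labelled descriptive, and do not rest the generalisability statement on them.

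The cost is plan wording, slight extra analysis and a negligible loss of precision, with no additional patients. It assumes that each patient's branch is known. The article does not say so explicitly, but a study run at three named sites should have it.

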### Outcome measures

The primary outcome is the occurrence of composite clinical endpoints (doubling of serum creatinine level, ESKD(eGFR < 15 ml/min for CKD 1–4 patients; or dialysis for at least 30 days or kidney transplant for patients with CKD 1–5), loss of renal function(≥ 40% decline in GFR from baseline), death(from any cause), major cardiovascular or cerebrovascular events) during the 5-year follow up (shown in Table 4) [44, 45]. Those outcome data will be collected through the outcome assessment scale during each visit by reviewing the laboratory test results and the medical record in Hospital Information System (HIS).

**Table 4 Tab4:** Definition of composite clinical endpoints

Clinical events	Definition
1.A doubling of serum creatinine levels	Doubling of the serum creatinine level from baseline sustained for at least 30 days according to central laboratory assessment
2.End-stage kidney disease (ESKD)	eGFR < 15 ml/min for CKD 1–4 patients; or dialysis or kidney transplant for CKD 1–5 patients
3.Loss of renal function	≥ 40% decline in GFR from baseline
4.Death	Death from any cause
5.Major cardiovascular or cerebrovascular events	Acute heart failure, myocardial infarction, ischemic cerebral infarction or intracranial hemorrhage

The main secondary outcomes include the absolute change and slope of eGFR, absolute changes of urinary protein creatinine ratio, 24-h urine proteinuria, intact parathyroid hormone level (iPTH), and self-management adherence rates (evaluated by self-management behavior questionnaire) and quality of life. Other outcomes include serum creatinine level (SCr), blood urea nitrogen level (BUN), plasma albumin, triglyceride, cholesterol, calcium, phosphate and other Laboratory markers and cardiovascular function.

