## Discussion

To the best of our knowledge, this is the first theory-based self-management cohort conducted in Mainland China for CKD patients. This paper presents the protocol for the design and process evaluation of this self-management cohort. We believe there are several elements in the design and implementation of this study that allow advantages for quality data to inform the management of CKD in China.

Previous studies have regarded self-management as a plausible way to slow CKD progression [20]. However, due to the short follow-up time, their results have certain limitations. This is because self-management adherence is high in these studies, but patients experience ‘active’ self-management initially whereas self-management behavior is neglected as time progresses [50]. Meanwhile, applying self-management to CKD management needs flexible appointments and re-planning options between nephrologists and patients which is more suitable to achieve by cohort research. Therefore, it is worthwhile to study the effect of self-management through a long-term follow-up in a real-world medical environment.

However, it’s not easy to maintain patients’ compliance in the long-term follow-up study. Results from other studies showed theory-based intervention can improve medication and self-management adherence in other chronic conditions [51, 52]. Guidelines also recommend the explicit use of behavior change for addressing lifestyle risk factors when designing and reporting interventions for patients with CKD [53, 54]. In this cohort, behavior change is based on the SCT framework [55]. The application of this theory has shown positive effects on health behaviors in many chronic disease settings such as diabetes, heart disease and neurological disorders [56, 57]. According to this theory, this cohort study will determine the specific items to personalize educational content and behavior change strategies based on psychosocial determinants of self-efficacy, self-regulation, skill mastery, and outcome expectations. Health education and self-management programs focus not only on changing the patient’s awareness of the disease, but also on improving their personalized self-efficacy attainment strategies addressing motivation to change motivational enhancement strategies, behavior modification, and emotion management and stress management issues [58, 59].

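### Self-management trajectories are to be related to renal events with no exposure window that ends before the risk period, and mediation is to be judged by adding mediators to the models one at a time

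*Protocol article*

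**What the plan says.** The Statistical analysis plan section of the protocol article states "we plan to perform three separate analyses for the primary outcome". The first is a chi-squared test and the second a log-rank test with a Cox or competing-risk model. For the third, "growth mixture models and group-based trajectory models (GBTM) will be used to analyze the trajectories of exposure and outcome variables". The purpose is given elsewhere: in the abstract, "the association between longitudinal trajectories of self-management and renal outcomes will be evaluated", and in the Discussion, where the long follow-up is valued because it lets the investigators "study the relationship among longitudinal trajectories of exposure, surrogate markers, and renal outcomes".

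On observation time, the Study design section says "All the patients will be followed for at least 5 years, or until the occurrence of a primary outcome", and Outcome measures counts composite endpoints "during the 5-year follow up".

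On mechanism: "Mediation will be analyzed by adding the hypothesized mediators, one by one, to the confounder-adjusted models".

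The article names no exposure window, lag, landmark, time-varying exposure or joint model, no rule for assigning patients to classes, and no time at which mediators are measured. The sensitivity analyses it names are the E-value and unspecified advanced models.

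**The concern.** Adherence can be observed only while a patient is event-free, and events are counted in the same five years. A patient with an early event contributes few visits, so the class assigned to that patient partly reflects event time rather than behaviour. The article supplies the conditions for this. It says of earlier studies that "self-management behavior is neglected as time progresses", so a lapse takes time to be seen. Its Background also accepts that clinical status and participation shift together during a study and that this can bias conclusions, so worsening disease may change behaviour shortly before an event.

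Mediation raises a related but separate problem. A mediator of enrolment must arise after enrolment. Putting it into a model whose clock starts at baseline leaves the order of mediator and event unclear, and factors that affect both mediator and event are not dealt with. Objectives ii (longitudinal relationship to surrogate markers and renal outcomes) and iii (working mechanism) rest on these two steps.

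**Working it through.** **The plan's own figures (Sample size calculation).** 30 variables × 10 events = 300 events, as stated. At 60 per 1,000 person-years with a constant hazard, 1,200 × (1 − exp(−0.06 × 5)) = 311 events. The gap between 300 and 311 does not bear on this point; 311 is used below because the simulation has a constant hazard and no drop-out.

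**Trajectory check under the null.** Inputs from the article: 1,200 patients, hazard 0.06 per year, 5 years, visits every 6 months (the stage 1–2 schedule), observation stopping at the event. Assumptions: two behaviour classes with equal hazard; a sustained class with mean score 0.7; a declining class falling linearly from 0.7 to 0.3; within-person SD 0.15; class parameters known. A patient is called sustained if Σ over observed visits of [log f(sustained) − log f(declining)] + log(p/(1 − p)) > 0, where p is the sustained proportion. A Cox model is then fitted on class. The true hazard ratio is 1.

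| p | All visits, modal class: HR (type I error) | 12-month landmark: HR (type I error) |
|---|---|---|
| 30% | 0.54 (0.998) | 0.97 (0.043) |
| 50% | 0.80 (0.485) | 1.00 (0.035) |
| 70% | 1.85 (0.995) | 1.02 (0.043) |

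The mechanism explains the direction. With few visits the data barely distinguish the classes, so the prior term decides and early-event patients fall into the larger class. That class collects the excess events. The 50% row needs a caveat. The two curves coincide at baseline, so a patient seen only at baseline is an exact tie, and the rule sends ties to the declining class. About 1,200 × (1 − exp(−0.03)) = 35 patients have an event before the first 6-month visit. With ties split at random, a re-run gave a hazard ratio of about 1.00. The bias therefore comes from unequal class sizes combined with hard assignment.

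**Reverse causation.** The score is lowered by 0.1 or 0.2 in the year before the event, with p = 50%.

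| Score drop | All visits | 1-year landmark | 2-year landmark |
|---|---|---|---|
| 0.1 | HR 0.42 | HR 0.76 | HR 0.75 |
| 0.2 | HR 0.21 | HR 0.64 | HR 0.62 |

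A landmark reduces this bias but does not remove it.

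**Cost of a 12-month landmark.** Events before month 12: 1,200 × (1 − exp(−0.06)) = 70, leaving 311 − 70 = 241. If adherence is recorded at each scheduled visit, stage 1–2 patients have three values by then (months 0, 6 and 12).

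**Mediation.** Inputs: 1,200 patients, half enrolled, baseline hazard 0.06 per year, enrolment HR 0.75. Enrolment and an unmeasured factor U both shift the mediator, and the mediator has no effect on the event. Share explained = (b₀ − b₁)/b₀, where b₀ and b₁ are the log hazard ratios for enrolment without and with the mediator, taken before rounding.

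| Log HR of U | HR without mediator | HR with mediator | Share explained |
|---|---|---|---|
| 0 | 0.74 | 0.74 | 0% |
| −0.3 | 0.73 | 0.82 | 35% |
| −0.6 | 0.75 | 0.92 | 72% |

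The true share is 0% in every row.

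**The case against.** The strongest reply is that the article never says classes are formed from the whole follow-up. The quoted sentence says only that trajectories will be analysed, and window, lag and assignment rule are details that a condensed article may leave to a full protocol or SAP. This stands in part. A reader might infer that the bias is built in, but the documents support only that it is left open. Whole-follow-up use is still the natural reading of the abstract and Discussion, and none of the named safeguards addresses timing: the E-value concerns unmeasured confounding.

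Second, the bias does not belong to trajectory models as such. On the same whole-follow-up null data, weighting by posterior class probability instead of assigning the modal class gave hazard ratios of 1.01, 0.99 and 0.99. This stands, with the limit that those runs contain no reverse causation.

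Third, a reader might size the problem from cruder groupings. Under the null, labelling patients persistent or lapsed gives hazard ratios of 2.4 to 3.5, and splitting on total sessions gives 0.20. The plan proposes neither, so those figures do not measure this point.

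Fourth, a landmark discards late lapses, which are the reason given for a long study, and three measurements describe a trajectory poorly. This stands, and it is why a landmark should not be the main remedy.

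Finally, it is tempting to call the mediation step another case of immortal time. The check does not support that: nothing was spuriously explained without a mediator-outcome confounder. Nor does the article say that the one-by-one contributions will be summed, so double counting cannot be asserted.

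**Conclusion.** The concern holds in a limited form. The plan commits to relating trajectories to events, ends observation at the event, and states no step that places exposure before the risk period. Followed as naturally read and with modal class assignment, it can produce a clear but false association. In the illustrative setting the hazard ratio ran from about 0.54 to 1.85 with no true effect, and the direction depended on which class was larger. These sizes rest on assumed adherence curves, known class parameters and no drop-out. That outcome-dependent observation can distort hard class assignment does not rest on the particular curves.

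Reverse causation is plausible on the article's own account, but its size here is unknown. The mediation fault is one of temporal order and mediator-outcome confounding, and the 35% to 72% is likewise illustrative.

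A reader might infer that the effectiveness result is compromised. On this point it is not: the chi-squared and log-rank/Cox comparisons of enrolled with control patients do not use trajectories.

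**What to change.** **Trajectory–outcome association.** As the main analysis, use adherence as a lagged time-varying exposure with inverse-probability weights built from earlier clinical status and earlier adherence, or fit a joint longitudinal-survival model. Later lapses then still count. Reverse causation is addressed as far as the lag and the measured variables capture it.

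**Supporting analysis.** Add a landmark analysis, for example classes from months 0–12 and events afterwards in patients still event-free. In either analysis, do not treat the modal class as known; carry the posterior class probabilities forward.

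**Mediation.** Replace the one-by-one addition with a counterfactual mediation method. Use mediators measured at a fixed time before the risk period, adjust for their baseline value and for named mediator-outcome confounders, and take mediators on one causal chain jointly.

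**Cost.** Analysis-plan wording and more analysis work. The landmark analysis leaves about 70 of 311 expected events unused and has only about three adherence measurements by month 12 in stage 1–2 patients.
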